### Blinding

The independent observer who is responsible for all measurements will be blinded to the treatment allocation. The trial participants will be aware of the treatment that they receive, but will not know the content of the treatment in the control group. The *PT-Prepare* will not be blinded since she is delivering the treatment for Group A.

### Intervention

Group A (*n* = 55) will be treated using the PREPARE protocol. Group B (*n* = 55) will receive conventional care, including general advice to stay active before surgery. Figure 2 presents an overview of the intervention groups.

**Fig. 2 Fig2:**
[figure not shown]
Overview of the intervention groups

#### Group A

The PREPARE protocol includes four individually tailored treatment sessions before surgery, and one booster session over the telephone two weeks after surgery. Depending on the patient’s schedule, PREPARE typically starts about 8 to 12 weeks *before* surgery. Each treatment session lasts for about one hour, and the post-surgery booster session lasts about 30 min. The intervention will be delivered by a physiotherapist with 1.5 years of CBT training. Figure 3 presents a schematic overview of the intervention.

**Fig. 3 Fig3:**
[figure not shown]
Overview of the intervention

##### Session 1 – Person-centred analysis of functioning

The aim of session 1 is to perform an analysis to identify the patient’s ability to stay active despite pain.*Cognitive interview with a Socratic approach* The patient participates in a cognitive interview aimed at capturing the patient’s cognitions and feelings relating to staying active despite pain. To direct the interview’s focus towards functioning rather than pain, the *PT-prepare* will discuss with the patient what kinds of physical activities he/she wishes to be able to perform after surgery.*Modified PHODA – analysis of activity behaviour* To capture the patient’s cognitions and feelings regarding activity behaviours related to physical activities and the underlying motives of these behaviours, a modified version of the Photograph Series of Daily Activities (PHODA) will be used (described below) [39], which is extended to include additional photographs of leisure-based physical activities.*Homework* Homework will be assigned with a two-fold aim: to help the patient learn to be aware of cognitions, feelings, behaviour, and body sensations related to a physical activity; and to increase or maintain his/her physical activity level. The patient will first make a list of physical activities that he/she would like to do, but has stopped performing or has been performing less often or less intensely due to his/her back problem. The patient will then select one of these physical activities, and monitor his/her cognitions, feelings, behaviours, and body sensations related to that physical activity as homework until session 2.*Identifying psychological risk factors* Questionnaires will be used to identify psychological risk factors for low functioning. Before session 2, the patient will complete the following questionnaires: Pain Catastrophizing Scale, Tampa Scale for Kinesiophobia and Self-efficacy for Exercise (described below).

##### Session 2 – Educational session

The aim of session 2 is to increase the patient’s knowledge regarding pain and the association between activity-related behaviours and underlying motives for these behaviours and form an individualised health plan.*Follow-up of homework* The session will start with a discussion of the patient’s cognitions, feelings, behaviours and body sensations related to the physical activity that he/she has monitored as homework.*Pain education* The patient will participate in an educational session about acute and chronic pain [40]. The theoretical underlying model for this pain education is the fear avoidance model presented by Vlaeyen et al. [19] and modified by Woby et al. [33]. The pain education session will be conducted as a dialogue between the *PT-prepare* and the patient, with the *PT-prepare* considering the patient’s thoughts, beliefs and knowledge as well as what he/she wants to know about staying active despite pain in relation to his/her pain condition. The session will be guided by the patient’s responses to the questionnaires completed after session 1, as well as the information from the patient’s homework assignment. This will help the *PT-prepare* to form a health plan together with the patient and decide upon a person-centred goal in relation to the underlying theoretical models of the intervention.*Goal setting – short-term goal* The patient will choose a person-centred short-term goal related to functioning that he/she will aspire to achieve before surgery. This short-term goal should be specific, measurable, achievable, realistic and time-targeted (SMART-goal) [41] and should involve a physical activity that is important to the patient. For example, a short-term goal could be to “*go for a walk in the nearby forest for 30 min every day*”. The patient will be encouraged to work towards the goal in gradual steps to enhance his/her self-efficacy related to that physical activity.*Homework* The homework assignment will have a three-fold aim: for the patient to learn to be aware of cognitions, feelings, behaviours and body sensations related to a physical activity; for the patient to increase his/her physical activity level, and finally to help the patient reach his/her short-time goal before surgery. The patient will choose this physical activity from the list of physical activities that he/she established during session 1.

##### Session 3 – Cognitive behavioural experiment

The aim of session 3 is to challenge the patient’s cognitions and feelings regarding performing physical activity despite pain while conducting a behavioural experiment.*Follow-up of homework and short-term goal* This session will start with a discussion of the patient’s progress towards their short-term goal, as well as their cognitions, feelings and behaviours related to the physical activity that he/she has performed as homework.*Cognitive behavioural experiment* Under the supervision of the *PT-Prepare*, the patient will perform a behavioural experiment aiming to enhance inhibitory learning by testing and violating negative expectations that the patient might have regarding a physical activity. For the behavioural experiment in this session, the patient will select one physical activity from the list of physical activities established during session 1. Before the behavioural experiment, the patient will be asked about what cognitions he/she has about the activity and what he/she expects will happen when performing that physical activity. After performing the physical activity, the validity of the patient’s thoughts and the patient’s level of self-efficacy will be discussed in terms of both short- and long-term consequences.*Homework* The three aims of the homework will be for the patient to learn to be aware of cognitions, feelings, behaviours and body sensations related to a physical activity, to increase his/her physical activity level, and to help the patient reach his/her short-term goal before surgery. The homework will be either the same physical activity selected during session 2, or a new physical activity from the list of physical activities established during session 1.

##### Session 4 – Goal setting after surgery

The aim of session 4 is to enhance the patient’s self-efficacy related to their short-term goal and to formulate two functioning-related goals to be reached at 4 and 8 weeks after surgery.*Follow-up of homework and short-term goal* This session will start with a discussion of the patient’s progress of his/her short-term goal and of the patient’s cognitions, feelings and behaviours related to the physical activity that he/she has performed as homework.*Goal setting – 4 and 8 weeks after surgery* The patient will choose two functioning related goals to reach at 4 and 8 weeks after surgery, which should involve a physical activity that is important to the patient. These goals will be set as SMART-goals [41].*Enhance self-efficacy related to short-time goal* The patient will be encouraged to continue working towards his/her short-term goal, and will be advised to take gradual steps towards enhancing his/her self-efficacy related to that goal. If the patient has already reached the short-term goal, the goal will be modified by increasing the intensity, duration, or frequency of the physical activity or by choosing another physical activity that the patient considers to be important.

##### Session 5 – Booster session

The aim of session 5 is to detect fear-avoidance beliefs and to increase the patient’s self-efficacy in relation to his functioning goals for 4 and 8 weeks after surgery. This session acts as a booster session that will be held over the phone at two weeks after surgery.*Cognitive interview with a Socratic approach* The patient will participate in a cognitive interview that aims to capture his/her cognitions and feelings regarding physical activities – particularly activities of daily life (ADL). The *PT-prepare* will identify tendencies towards fear-avoidance beliefs and encourage the patient to stay active.*Follow-up of goals 4 and 8 weeks after surgery* The patient’s goals will be discussed and will be adjusted with regards to duration, intensity, or frequency in accordance with the patient’s current medical status.*Enhance self-efficacy related to goals 4 and 8 weeks after surgery* The patient will be encouraged to continue with his/her progress towards the goals, and will be advised to take gradual steps towards enhancing his self-efficacy related to that physical activity.

#### Group B

Patients in Group B will receive a conventional care intervention. Before surgery, these patients will be encouraged to contact a physiotherapist at one of the private spine clinics to schedule an informational session. There, they will be provided with basic information about the upcoming surgery, and told about the types of core exercises that will be introduced at the ward post-surgery. The physiotherapist will encourage the patients to stay active and to start performing the recommended exercises prior to their surgery.

#### Common features for Group A and B after surgery

The aim of this trial is to evaluate the effects of PREPARE rather than the postoperative treatment of the patients in Group A. Both groups will receive the same post-surgical treatment, aside from the booster session for Group A. After surgery, the patients will meet with a physiotherapist at the ward, and participants in both groups will receive the same information regarding post-operative rehabilitation. At the ward, both groups will be instructed to perform the same home exercise program comprising core stabilisation exercises for the first four weeks after surgery. All patients will be advised to stay active on a daily basis, and to contact a physiotherapist from a rehabilitation centre or physiotherapy clinic in their local area at four weeks after the surgery to continue their rehabilitation. The content of this rehabilitation will be determined by the treating physiotherapist and will not be controlled for.

### Outcome measures

#### Primary outcome measure

Disability will be measured using the revised version (version 2.0) of the Oswestry Disability Index (ODI). In the ODI, patients rate their perceived disability on 10 items relating to pain intensity, personal care, lifting, walking, sitting, standing, sleeping, sex life, social life and traveling Each item is scored from 0–5, with 0 indicating the least amount of disability and 5 the most severe disability. The scores are summed to generate a total score ranging from 0 to 100, with 0 indicating no disability. The English version of the ODI shows high internal consistency [42] and test–retest reliability [43], as well as adequate content validity and responsiveness [44] for patients with CLBP.

#### Secondary outcome measures (effect evaluation)

Patient-reported functioning will be measured using the Swedish version of the Patient-Specific Functional Scale (PSFS). In the PSFS, the patient lists three activities that are limited by the condition for which he/she is seeking treatment. The patient then rates their perceived difficulty in performing each of the listed activities on a scale from 0 to 10, with 0 indicating that the patient cannot perform the activity at all. The three separate scores are averaged to generate the total score The English version of the PSFS is responsive to clinically important change over time [45], and shows good test–retest reliability and strong criterion validity [46] for patients with CLBP.Performance-based functioning will be measured using five tests: 5-min walking (measurement of the distance the patient can walk in 5 min); 50-feet fast walking (measurement of the time it takes for a patient to walk 50 feet as fast as possible); the Timed up-and-go (measurement of the time it takes for a patient to arise from a chair, walk three meters, turn around, walk back to the chair and sit down); 1-min stair-climbing (measurement of the number of steps the patient can climb in one minute) [47, 48]; and the One-Leg Stand Test (measurement of the duration the patient can stand on one leg, with eyes open and with eyes closed) [49]. Findings support the construct validity of these tests and show that they have adequate test–retest reliability for patients with CLBP [47–49].A digital triaxial accelerometer (ActiGraph GT3X+; ActiGraph, Pensacola, FL, USA) will be used to assess physical activity as steps per day, time spent at different intensity levels and time spent sedentary [50, 51]. The GT3X+ measures acceleration in three planes and the raw output is “counts”. Based on the number of counts per minute, the raw output is classified into time spent at different intensities of physical activity and time spent sedentary by using appropriate cut-points in the complementary software, Actilife 6 (ActiGraph, Pensacola, FL, USA). The device will be attached with an elastic band to the patient’s right iliac crests during waking hours for a 7-day period. The patient will be instructed to remove the device while sleeping, swimming and bathing. The GT3X+ has shown high construct validity when measuring physical activity intensity levels [50] and excellent criterion validity when measuring the number of steps [51] in healthy adults.Health-related quality of life will be measured using the Swedish version of the European Quality of Life 5 Dimensions Questionnaire (EQ-5D). In the EQ-5D, patients rate their health on five items relating to mobility, self-care, usual activities, pain/discomfort and anxiety/depression. The patient also rates his/her general health on a visual analogue scale. The English version of the EQ-5D has acceptable test–retest reliability and findings support its construct validity for patients with chronic musculoskeletal pain [52].Health-related quality of life will also be measured using the Swedish version of the Short Form (36) Health Survey (SF-36). The SF-36 comprises eight scaled sections: vitality, physical functioning, bodily pain, general health perceptions, physical role functioning, emotional role functioning, social role functioning and mental health [53]. The Swedish version of the SF-36 shows high internal consistency and high discriminant validity and findings support its construct validity in a Swedish population sample [54].Back and leg pain intensity levels over the last week will be measured using 100-mm Visual Analogue Scales (VAS) [55]. Findings support the validity and reliability of the VAS in patients with chronic pain [56].Pain will also be measured using a 5-point scale with the following response options: pain-free, much better, better, unchanged, or worse. This scale shows good responsiveness for patients with CLBP undergoing lumbar fusion surgery [57].Pain catastrophizing will be measured using the Swedish version of the Pain Catastrophizing Scale (PCS), which includes 13 items assessing catastrophizing thoughts about pain. The PCS has shown adequate internal consistency and high construct validity in a Swedish population sample [58].Kinesiophobia will be subjectively rated using the Swedish version of the Tampa Scale of Kinesiophobia (TSK-SV). The TSK comprises 17 items assessing the subjective kinesiophobia rating. The TSK-SV has shown high test–retest reliability and internal consistency, and has support for its face, content and construct validity in patients with CLBP [59].Self-efficacy related to exercise will be measured using the Swedish version of the Self-Efficacy for Exercise scale (SEE-SV). On the SEE-SV, the patient rates his/her confidence that he/she could exercise three times per week (20 min each session) under nine different conditions – for example, “if you experienced pain while you exercised” or “if you felt tired”. The SEE-SV shows substantial test–retest reliability and satisfactory internal consistency and content validity for older adults [60].Anxiety and depression will be assessed using the Swedish version of the Hospital Anxiety and Depression Scale (HADS) [61]. In a Swedish population sample, the HADS showed moderate internal consistency and high construct validity [62].Satisfaction with treatment results will be measured using a 3-point scale with the following response options: satisfied, uncertain, or dissatisfied.PHODA is an instrument that is conventionally used to determine the perceived harmfulness of daily activities in patients with LBP [39]. In this trial, we will use a modified version of PHODA to capture the patients’ beliefs and attitudes regarding activity behaviour, rather than the expected harmfulness. The original PHODA is extended with photos of leisure-based activities that the patient is also asked to rate in the above-described manner. The modified PHODA will not be used to measure outcomes of the present trial, but will rather be employed as a tool to supply the *PT-prepare* with information about the patient’s activity behaviour in relation to the pictured physical activities and the motives underlying the activity behaviour.

#### Secondary outcome measures (economic evaluation)

Healthcare costs and to value production loss will be measured using a self-reported custom-made health economic questionnaire.

### Data collection

Data collection for the patient-reported outcome measures will take place at baseline (8–12 weeks before surgery), at 1 week before surgery; and at 3 weeks, 8 weeks, 3 months, 6 months, 1 year, 2 years and 5 years after surgery. Each participant will have a special numeric code, and all data will be stored in a fireproof cupboard and on a password-protected computer at one of the spine clinics. Double data entry and missing data in the questionnaires will be checked as soon as the participant has done the follow-up by an independent trial coordinator. Figure 4 presents details of the follow-up sessions.

**Fig. 4 Fig4:**
[figure not shown]
Overview of the baseline and follow-up sessions. EQ-5D, EuroQol 5 Dimensions Questionnaire; HADS, Hospital Anxiety and Depression Scale; ODI, Oswestry Disability Index 2.0; PCS, Pain Catastrophizing Scale; PSFS, Patient-Specific Functional Scale; QoL, quality of life; SES-SV, Self-efficacy Scale for Exercise; TSK, Tampa Scale for Kinesiophobia; SF-36, Short Form (36) Health Survey; VAS, Visual Analogue Scale of Pain

### Analyses

#### Sample size

The number of participants (*n* = 110) was determined based on a power analysis (80 % power, alpha = 0.05), with disability measured with ODI as the primary outcome. We determined that we required a sample size of 55 patients in each group to show a statistically significant between-group difference of at least 8 points in the ODI with a standard deviation of 15 based on earlier studies [57, 63]. The difference of 8 points on the ODI was based on the previously reported minimal clinically important difference within the range of 5.2–16.3 where 10 points are mostly used for the ODI in a similar population [57, 64].

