**Methods/Design:**

We will recruit 110 patients between 18–70 years of age with degenerative disc disease who are waiting for lumbar fusion surgery. These patients will be randomly assigned to receive either PREPARE or conventional care. PREPARE uses a person-centred perspective and focuses on promoting physical activity and targeting psychological risk factors before surgery. The primary outcome will be disability measured using the Oswestry Disability Index 2.0. Secondary outcomes will include functioning (patient-reported and performance-based), physical activity (accelerometer), health-related quality of life, back and leg pain intensity, pain catastrophizing, kinesiophobia, self-efficacy, depression, anxiety, satisfaction with treatment results and health economic factors. Data will be collected at baseline (preoperatively) after the intervention (preoperatively), 3 and 8 weeks, 3, 6, 12, 24 and 60 months postoperatively.

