### Participants

We will recruit a total of 110 patients of 18–70 years of age, who have major complaints of DDD: CLBP of motion-elicited type degenerative changes of 1-3 segments of the lumbar spine, reproducible pain in clinical examination assessed to originate in the same segment as demonstrating degenerative changes, and on the waiting list for lumbar fusion surgery. Patients may have additional minor radiating symptoms with or without simultaneous surgical procedure for disc herniation, foraminal decompression, or isthmic spondylolisthesis. The trial will exclude patients who have undergone previous decompression surgery for spinal stenosis or who have spinal malignancy, dominating radiculopathy, a confirmed neurological disorder or rheumatic disorder, deformities in the thoracolumbar spine (e.g. idiopathic scoliosis), or a poor understanding of the Swedish language.

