### Recruitment and randomization

Trial participants will be recruited from two private spine clinics and one university hospital. Patients will be clinically examined by an orthopaedic surgeon, who will make a medical diagnosis based on the clinical and radiological findings. Patients who are diagnosed with DDD will be informed that lumbar fusion surgery is a treatment option. When a patient agrees to undergo surgery and is placed on the waiting list, the hospital and the spine clinics coordinators will inform the physiotherapist (*PT-prepare*) who will deliver the trial intervention. Then the *PT-prepare* will call the patient to inform him/her of the trial and invite him/her to participate.

Patients interested in participating will meet with an independent observer at baseline, 8–12 weeks before surgery at one of the private spine clinics. The independent observer will once again provide the patient with information about the trial. If the patient agrees to participate, he/she will sign an informed consent form provided by the independent observer. The independent observer will then guide the participant through the functional capacity testing and provide him/her with the patient-reported outcome measures and the accelerometer. After this, the independent observer will give the participant a sealed envelope containing the group allocation.

The participant will be randomly allocated to Group A or Group B using a computerised random list with no restrictions, arranged by an independent statistician. The project leader – who will not take part in the intervention and outcome assessments – will be responsible for arranging sequentially numbered, opaque, sealed envelopes. To conceal the group allocation, the participant will not open this envelope in the presence of the independent observer. The allocation list will be stored in a locked fire-proof cupboard at the university laboratory, in accordance with the principles of the ethical approval.

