#### Health economics

For our health economic analysis, a societal viewpoint will be used. Indirect and direct healthcare costs will be measured using a self-reported custom-made health economic questionnaire. Days of hospital stay will be determined from patient charts. Intervention costs will be calculated for each patient – including the number and duration of treatments for the 55 patients who will receive PREPARE. We will compare the mean total costs between the therapy groups. The cost prices of medical consumption will be calculated. All costs will be presented in euros. The human capital approach will be used to calculate productivity costs.

We will use these data to perform a cost-effectiveness analysis and cost-utility analysis. For the cost-effectiveness analysis, an incremental cost-effectiveness ratio (ICER) will be calculated, weighing total costs against disability levels (ODI). For the cost-utility analysis, utility will be calculated from EQ-5D scores for every assessment. Mean total costs will be weighed against mean health utility, i.e. comparing cost per Quality Adjusted Life Years (QALY) gained.

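### The number recruited equals the number required, so the stated 80% power holds only if essentially every randomised patient provides a 6-month ODI

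*Protocol article*

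**What the plan says.** All of this is in the protocol article.

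- **Sample size:** the number of participants "was determined based on a power analysis (80 % power, alpha = 0.05"), with the ODI as primary outcome. The section continues: "We determined that we required a sample size of 55 patients in each group to show a statistically significant between-group difference". The target effect and its assumed spread are then specified as "at least 8 points in the ODI with a standard deviation of 15 based on earlier studies".
- **Abstract (Methods/Design) and Participants:** "We will recruit 110 patients" and "We will recruit a total of 110 patients of 18–70 years of age". This is 2 × 55, with nothing added.
- **Recruitment and randomization:** consent, baseline and allocation take place 8–12 weeks before surgery. Patients are "randomly allocated to Group A or Group B using a computerised random list with no restrictions".
- **Intervention and Health economics:** each group is given as 55; the latter refers to the "number and duration of treatments for the 55 patients who will receive PREPARE".
- **Effect evaluation:** the ODI at 6 months is compared by two-sample t-test or Wilcoxon rank sum test under intention to treat. A random-intercept linear mixed model is also named for the repeated measures.
- **Data collection:** questionnaires are to be checked for missing data. No expected rate of missing outcomes is given in any section.

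**The concern.** A power calculation gives the number of patients who must contribute an outcome to the test. Here that number is also the number enrolled. A patient who withdraws, does not have the operation or does not return the 6-month ODI therefore takes the comparison below the size that the article itself calls required. Intention to treat governs the group in which a patient is analysed; it does not supply a missing ODI to a t-test.

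What is at stake is how the result is read. A null primary result would be judged against a claimed type II error risk of 20%, when for the named test it could be 25–30% under unremarkable loss. Bias and type I error are not at issue.

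**Working it through.** **Inputs from the Sample size section.** Difference 8, SD 15, alpha 0.05, power 80%, 55 per group. Sidedness is not stated. Two-sided is assumed because it reproduces the figure; a one-sided test would need only 44 per group.

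**Step 1: reproduce the stated number.** Normal formula: n = 2 × (1.960 + 0.842)² × 15² / 8² ≈ 55.2 per group. At n = 55 the power is 79.9% by the normal approximation. By the noncentral t distribution, which matches the planned test, it is 79.2% at 55, 79.9% at 56 and 80.6% at 57. The stated 55 is thus reproduced to within a point, with equal groups and no allowance for loss.

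**Step 2: power after loss.** With a fraction d lost equally from both groups, n = 55 × (1 − d), the noncentrality is 8 / (15 × √(2/n)), and the degrees of freedom are 2n − 2. The article gives no d, so a range is assumed.

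| Assumed loss | n per group | Noncentrality | t-test power | Difference detectable with 80% power |
|---|---|---|---|---|
| 0% | 55 | 2.80 | 79.2% | 8.1 |
| 5% | 52.25 | 2.73 | 77.0% | 8.3 |
| 10% | 49.5 | 2.65 | 74.8% | 8.5 |
| 15% | 46.75 | 2.58 | 72.3% | 8.8 |
| 20% | 44 | 2.50 | 69.6% | 9.1 |

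**Step 3: the unrestricted list, as a side check.** With 110 patients allocated independently at 1:1, an exact 55/55 split has probability 7.6%, and the 95% range for one group is 45–65. With all 110 evaluable, power is 78.8% at 50/60 and 77.8% at 45/65. Averaged over all splits it is 78.8%, which is 0.4 points below the 79.2% at 55/55.

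**Step 4: what adjustment for baseline ODI could recover.** If the correlation between baseline and 6-month ODI is r, the residual SD is 15 × √(1 − r²). The article gives no r, so a range is assumed.

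| Assumed r | Residual SD | Power, 10% loss | Power, 20% loss |
|---|---|---|---|
| 0.3 | 14.3 | 79% | 74% |
| 0.4 | 13.7 | 82% | 77% |
| 0.5 | 13.0 | 86% | 81% |
| 0.6 | 12.0 | 91% | 87% |

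Adjustment can restore 80%, but not throughout this range: at r = 0.3 it falls just short at 10% loss, and at r = 0.4 it falls short at 20% loss.

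**The case against.** **The size rests on assumed loss.** This is true. Without any loss, the shortfall that can be shown from the article is under one point. What does not depend on an assumption is that recruited equals required, and hence that there is no margin. A condensed article may leave the handling of missing data to a fuller document, but such a document cannot add recruits to a stated 110 without changing that number.

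**The mixed model may recover power.** It may, since it can use partly followed patients, and the article does not say that the analysis is restricted to patients with a 6-month ODI. But the power statement does not rest on that model, no correlation is given, and baseline is not named as a covariate. This lowers the severity; it does not remove the point.

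**Eight points is a cautious target.** The article notes that 10 points is the value mostly used. At a true difference of 10, t-test power is still 90.7% at 10% loss and 87.1% at 20%. This too argues for moderate severity. The 80% claim, however, was made for 8 points.

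**Stronger readings that a reader might infer.** One is that the sample size is miscalculated because 55.2 was rounded down. The effect is under one point, and an SD of 14.84 instead of 15 would give exactly 80%, so this is not an arithmetic error. Another is that the unrestricted list seriously weakens the trial because 55/55 is improbable. The average cost is 0.4 points, and the 55 under Intervention reads naturally as a planned size. A third is that baseline adjustment makes extra recruitment unnecessary. The article gives no correlation on which to base that, and the second table shows cases where it would be wrong.

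**Conclusion.** The point holds in a limited form. The stated 80% power applies to a trial in which essentially all 110 randomised patients provide a 6-month ODI, and the plan has no margin for anything less. For the planned t-test, the cost is about 2 points of power at 5% loss and about 10 points at 20% loss, measured from 79.2% with complete data. This assumes a two-sided test, equal loss in the two groups, the article's own difference and SD, and loss rates that are illustrative. Rounding and group imbalance show only that there is no slack elsewhere to absorb the loss. Severity is moderate: a stated design property is more favourable than the design supports, but the validity of the comparison is not affected.

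**What to change.** In the Sample size section, replace the single power figure with power against 6-month completion for the t-test: about 79, 77, 75, 72 and 70% at 0, 5, 10, 15 and 20% loss, with detectable differences of 8.1, 8.5 and 9.1 points at 0, 10 and 20%. State the loss that the sponsor expects. There and under Intervention and Health economics, describe 55 as the expected group size.

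If the sponsor wants to keep an 80% claim, name an analysis adjusted for the baseline ODI, which is already collected, as the basis of the power. State the assumed correlation and its source, and show the range in the second table.

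The cost is rewording and a stated power that looks less favourable. Restating the power does not itself change recruitment, treatment or data collection.
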